The computer-based exercises to be performed during each session are personalized to each participant’s cognitive needs, as identified by a neurocognitive evaluation and interview. Thus, participants are seen in a group but work on different exercises personalized to their needs. These exercises may target several cognitive domains such as visual and auditory attention, focused and divided attention, sustained attention, processing speed, verbal and visual working and long-term memory, planning, problem-solving, inhibition, and mental flexibility. The repetition of the exercises and the presentation of the results and the level of progress on the screen of each participant enable the reinforcement of autonomy and favor the use of errorless learning. Participants conclude their computer based cognitive activities for the day by completing a worksheet about the exercises completed, the level reached, the cognitive function worked on, the link with daily life. Further comments may pertain to the strategy used in each exercise, the benefit(s) of the session, and the difficulties encountered. These activities encourage self-reflection, metacognition and enhanced cognitive skillfulness to handle everyday situations.

The Bridging session manual used in France covers 34 sessions organized in 8 modules (Table 1).

**Table 1 tab1:** The NEAR France program modules.

	Title	Number of sessions
Module 1	Introduction to cognitive skills	7
Module 2	Verbal reasoning and problem solving	3
Module 3	Thinking about your own thoughts	5
Module 4	Planning and organization	4
Module 5	Attention	4
Module 6	Effective communication	8
Module 7	Healthy living	2
Module 8	Conclusion	1

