
### Study design

2.2.

Our study is a prospective, experimental, open, and non-randomized controlled trial.

This study research is carried out in the Child and Adolescent Psychiatry Department in Razi University Hospital-Manouba-Tunisia. It is conducted in collaboration with the C3RP team (Resource Center for Cognitive Remediation and Psychosocial Rehabilitation, Ile-de-France) -Sainte-Anne Hospital and under the supervision of [name] (Ph.D. – Professor of Psychology at Columbia University Irving Medical Center and Director of Cognitive Health Services for the New York State Office of Mental Health, United States).

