### Participants and screening

2.3.

The inclusion criteria are:

ο Adolescents aged than 13 years, meeting the Diagnostic and Statistical Manual for Mental Disorders (DSM-5) (4) criteria for ASD confirmed by the ADI-R [Autism Diagnostic Interview-Revised, (58)] criteria, without mental retardation, followed in the Child and Adolescent Psychiatry Department (out-patient clinic) in Razi University Hospital-Manouba-Tunisia. Patients who agreed to participate in our study were retained.ο Sufficient level of understanding and communication in Arabic and French (allowing them to understand the instructions during the care sessions).ο Regular school curriculum.

It should be noted that adolescents treated with psychotropics will be included, with the condition that there will be no change to the drug treatment (molecule, dosage) during the period of study.

A certified therapist will conduct a standardized interview for the clinical and diagnostic evaluation of these adolescents (using the ADI-R).

Parents obtained information concerning the study and had the opportunity to ask questions before agreeing to the participation of their children, and during the study.

The non-inclusion criteria are:

ο Out-of-school patientsο Mental retardation or severe cognitive impairmentsο A history of neurological disorderο Severe behavioral disordersο Electroconvulsive therapy in the past 6 months

Exclusion criteria are:

ο Non-achievement of the programο Missing more than three sessionsο Non-achievement of assessments after finishing the therapy

Strategies to improve adherence to intervention:

ο Method of choice: NEAR program enhances intrinsic and extrinsic motivation by employing more engaging and interesting exercises packages for cognitive practice, involving participants in choosing the focus of training.ο All candidates received two psycho-education sessions: one individual and one group session in order to raise their awareness, motivation and to present the program (number of sessions, progress, interest…).ο Parent involvement in the program and home tasks.

Our study will include 30 patients that will be divided into two groups: NEAR group/ control group (a group that will assign usual care).

This allocation of patients between the two groups would be made according to the following criteria:

ο Teenage motivationο Their availability and parent’s one to accompany them to their clinical evaluations and therapeutic sessions.

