The patients included in the NEAR group will be divided into three groups of five patients each. The rhythm for sessions for each group is one to two sessions per week. The duration of the program will be about 6 months.

In our study, the duration of the sessions will vary according to the capacities of the participants and the exchanges between them (about 90–120 min).

Two pre-trained therapists lead the sessions and are assigned to follow the progress of each participant.

All selected patients will have an assessment of global functioning, cognitive function (social cognition and neurocognition) pragmatic skills, social skills and self-esteem, and at baseline (T1), 1 week after the end of the NEAR program (T2), and 6 months later (T3). The same interval will be kept for three sessions of evaluations of the control group.

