Besides, anxiety and autism are often closely intertwined, this comorbidity is linked with significant functional impairment, and it can be related to a neurological response. Specific overlapping areas of the brain are likely involved in both the manifestation of autism and anxiety. For example, neural responses in the brain related to how a person processes rewards can be a risk factor for anxiety and a risk factor for autism (95). This anxiety may be manifested in intolerance and fear of change and uncertainty during the sessions and frustration at difficulty or failure in computerized cognitive exercises and so a quick change of exercises which can affect the effectiveness of the cognitive training. Finally, pharmacological therapy could have an effect on cognition and the chance to NEAR program response.

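### The post-treatment exclusion rules on programme completion and missed sessions can remove NEAR patients only, so NEAR adherers are compared with controls who faced no adherence filter

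*Protocol article*

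**What the plan says.** The protocol article describes the trial in these words: "Our study is a prospective, experimental, open, and non-randomized controlled trial". Section 2.3 (Participants and screening) gives inclusion criteria, then a screening list introduced by "The non-inclusion criteria are", and then a third, separate list of exclusion criteria: "Non-achievement of the programο Missing more than three sessionsο Non-achievement of assessments after finishing the therapy".

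On size and arms, the same section says: "Our study will include 30 patients that will be divided into two groups: NEAR group/ control group (a group that will assign usual care"). It continues: "The patients included in the NEAR group will be divided into three groups of five patients each". Controls have three evaluations at the same intervals as the NEAR group (T1, T2, T3). No programme or therapy sessions are described for them.

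On programme length, section 2.1.1 says: "The Bridging session manual used in France covers 34 sessions organized in 8 modules".

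Section 3 (Statistical analysis) names GAF and the BRIEF Global Executive Composite as primary outcomes and compares NEAR with control by a group-by-time repeated-measures ANOVA. It describes no analysis that keeps excluded patients in their group.

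**The concern.** None of the three exclusion items can be known at screening, so they act on patients already enrolled and, for the first two, already in treatment. The third takes effect once therapy is over. The list therefore cannot mean only that treatment stops; the natural reading is removal from the study data.

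A filter on adherence applied to one arm only makes the arms differ in a way the treatment did not cause. The article's Discussion expects some participants to show anxiety, difficulty with change and "frustration at difficulty or failure in computerized cognitive exercises". It is plausible, though the article does not say so, that the same difficulties lead to missed sessions and to less improvement. The NEAR patients removed would then tend to be those doing worst, while similar adolescents in the control arm stay in.

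Two things are at stake. The primary comparison can favour NEAR when there is no effect. It also answers a narrower question (the effect in those who attend nearly everything) than the stated objective, which is the effect of the programme on the functioning of adolescents with autism. This fault arises after allocation. It is separate from the allocation by motivation and availability and would persist if allocation were perfect.

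**Working it through.** The article gives no effect size, SD, power or dropout figure, so there is no calculation of its own to reproduce. Two counts can be checked, and both agree: 3 × 5 = 15 NEAR patients (leaving 30 − 15 = 15 controls), and Table 1's modules sum to 7 + 3 + 5 + 4 + 4 + 8 + 2 + 1 = 34 sessions.

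**Step 1: which arm can meet each rule**

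| Rule | NEAR | Control |
|---|---|---|
| Programme not completed | Yes | No: there is no programme |
| More than three sessions missed | Yes | No: there are no therapy sessions, and only three evaluations |
| Post-therapy assessments not done | Yes | Literally no; possibly yes if read as missing T2 or T3 |

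All candidates receive two psycho-education sessions, but two sessions cannot produce more than three absences. The first two rules therefore remove 0 controls by construction.

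**Step 2: how strict the threshold is.** With 34 sessions, a patient must attend at least 31 (31/34 = 91%). One who attends 30 (30/34 = 88%) is removed.

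**Step 3: how many NEAR patients could go.** Assumption: each session is missed independently with a common probability p. The chance of removal is P(X ≥ 4) for X ~ Binomial(34, p).

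| p (assumed) | P(X ≥ 4) | Expected of 15 |
|---|---|---|
| 0.03 | 0.018 | 0.3 |
| 0.05 | 0.088 | 1.3 |
| 0.08 | 0.288 | 4.3 |
| 0.10 | 0.446 | 6.7 |

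If the adapted programme had 36 sessions, p = 0.05 would give 0.104 and p = 0.10 would give 0.491.

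**Step 4: bias with no true effect.** Assumption: a normally distributed tendency to miss sessions correlates ρ with poorer change. Removing the worst-attending fraction f raises the mean change of those left by ρ·φ(z_f)/(1 − f), in SD units of change. Here z_f is the f-quantile of the standard normal distribution and φ is its density.

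| Removed | φ(z_f)/(1 − f) | ρ = 0.3 | ρ = 0.5 |
|---|---|---|---|
| 1 of 15 | 0.139 | 0.042 | 0.069 |
| 3 of 15 | 0.350 | 0.105 | 0.175 |
| 5 of 15 | 0.545 | 0.164 | 0.273 |
| 45% | 0.720 | 0.216 | 0.360 |

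At ρ = 0 the bias is 0.

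**Step 5: effect on the test.** With k removed, the standard error of the difference is √(1/(15 − k) + 1/15) SD. For k = 3 this is √(1/12 + 1/15) = 0.387; for k = 5 it is √(1/10 + 1/15) = 0.408. Dividing the bias by this and using a two-sided 5% normal test, the approximate type I error for ρ = 0.3 to 0.5 is:

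- 5.1% to 5.4% for k = 1
- 5.8% to 7.4% for k = 3
- 6.9% to 10.2% for k = 5

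The article does not say whether its 5% level is one- or two-sided; two-sided is assumed.

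**The case against.** Several points can fairly be made on the other side.

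- **The third rule may reach controls.** If it covers a control who misses T2 or T3, the control arm is not wholly unfiltered. This stands, and it limits the claim to the first two rules, which remain one-sided.
- **The link between absence and poor response is inferred.** The Discussion places anxiety and frustration within sessions and does not connect them to absence. Absences could instead reflect the parents' availability, in which case ρ, and the bias, could be near zero. This stands as a limit on size. Nothing in the article shows that the correlation is zero, and the design should not depend on it.
- **Absence may be rare.** NEAR patients are chosen partly for motivation and availability, and adherence measures are described. At 3% absence, fewer than one patient would be expected to go.
- **The model is simple.** It takes 34 sessions from the French manual, while section 2.1.2 amends Module 6 and the adapted total is not stated. It also uses one common absence rate, although patients will differ.
- **The bias is modest against the noise.** For three removals it is less than half the standard error of the difference.
- **Allocation already makes the arms differ.** Analysing everyone will not make the comparison unbiased. That is true, but it is no reason to add a second selection that probably pushes the same way.
- **An analysis plan could settle the population.** The article does not leave the point open: it fixes a removal rule, and that rule is the fault.

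**Conclusion.** The concern holds. The programme-completion and missed-session rules act after entry, can remove NEAR patients only, and feed directly into the primary NEAR-versus-control comparison. That conclusion rests on the text and needs no assumption.

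The size does need assumptions. For absence rates of 3% to 10% per session, the expected loss runs from about 0.3 to 6.7 of 15 NEAR patients. With ρ between 0.3 and 0.5, the bias towards NEAR runs from about 0.04 SD (one removed) to 0.36 SD (45% removed). It would be zero if absence were unrelated to outcome. Because the rule can bias the primary result of a 30-patient trial and is easy to replace, it should be corrected before analysis.

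**What to change.** Delete non-completion of the programme and the limit of three missed sessions from the exclusion criteria. State instead that every enrolled patient is assessed at T2 and T3 and analysed in the assigned group, whatever the number of sessions attended. Record sessions attended for each NEAR patient. Keep those who missed no more than three sessions as a labelled supportive analysis of NEAR completers. Make clear that a missed T2 or T3 assessment is treated as missing data in either arm, with counts and reasons reported by arm. This concerns who is assessed and analysed, not whether anyone should stop or continue the programme.

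The cost is a wording change and the effort of inviting low attenders to assessments already scheduled. No extra patients or procedures are needed. Fifteen adolescents were already reported under NEAR, so for anyone already removed the T2 visit may have passed. That loss should be reported, and T3 obtained where still possible. The estimated effect will probably be smaller because partial attenders are counted. With all patients retained, the bias from this rule is zero; confounding from the non-random allocation remains.

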## Statistical analysis

3.

Data collection and statistical analysis will be performed using the Statistical Package for Social Sciences (SPSS) version 25.

We will proceed to the comparison of the different scores of each group at the beginning and at the end of the study as well as to the comparison of the progression of the two groups between them at the beginning and at the end of the study.

The primary objective of our study is to facilitate the transfer of new skills to daily life and thus the global functioning of this population. Primary outcomes will be based on the GAF score and The Global Executive Composite score of the BRIEF. All other measures (social cognition, neurocognition, social skills, pragmatic skills and self-esteem) will be secondary outcomes and will be assessed descriptively.

For the descriptive statistics, we will calculate means and standard deviations for age and educational level and for categorical data, e.g., sex we will use Fisher’s Exact Chi-squared test.

For each neurocognitive and social cognition domain measure, we will conduct *t*-tests for independent samples to examine baseline differences for this sample. To examine Group X Time interaction for measuring treatment effects, we will conduct a Repeated Measure-Analysis of Variance (RM-ANOVA) that compared the difference scores of NEAR-group vs. Control-group at baseline and at the completion of the intervention.

A RM-ANOVA will also be used to examine differences in pragmatic skills, social skills and self-esteem.

For the two measures where there were statistically significant baseline differences, we will repeat the RM-ANOVA using baseline cognitive scores as a co-variate to control for baseline differences.

The significance level for all statistical analyses will be set to *p* = <0.05.

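### The exclusion for incomplete post-therapy assessments names no visit and no minimum data, so it allows patients with usable T1 and T2 primary scores to be dropped, and its application to controls is undefined

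*Protocol article*

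**What the plan says.** The Participants and screening section (2.3) keeps two lists apart. The non-inclusion criteria work at screening. The exclusion criteria work after enrolment, and there are three: the programme is not achieved, more than three sessions are missed, and "Non-achievement of assessments after finishing the therapy". The article does not say that an excluded patient stays in any analysis.

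The same section places the assessments at baseline (T1), "1 week after the end of the NEAR program (T2), and 6 months later (T3"). For controls, "The same interval will be kept for three sessions of evaluations of the control group". On size, "Our study will include 30 patients that will be divided into two groups", and "The patients included in the NEAR group will be divided into three groups of five patients each". Allocation is not random. It follows the adolescent's motivation and "Their availability and parent’s one to accompany them to their clinical evaluations and therapeutic sessions".

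The Statistical analysis section (3) states: "Primary outcomes will be based on the GAF score and The Global Executive Composite score of the BRIEF". All other measures are secondary. The Group by Time test for the treatment effect is a repeated-measures ANOVA on the "difference scores of NEAR-group vs. Control-group at baseline and at the completion of the intervention". That sentence does not name T3.

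**The concern.** The third exclusion criterion removes enrolled patients because follow-up data are incomplete, and its trigger is not defined. Two assessments follow the therapy, half a year apart, and each covers many instruments besides the two primary ones. Nothing limits the rule to T2 or to the primary measures. A patient whose T1 and T2 GAF and BRIEF are complete could therefore be excluded over a later visit or a secondary test that the primary comparison does not use.

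Two things are at stake. The first is precision, since with about 15 patients per arm each loss counts. The second is selection: whether a patient returns or finishes a battery may be related to functioning or family support, and so to the outcome. The trial is open, so an undefined trigger can also be settled after scores have been seen.

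The wording depends on completing a therapy that controls do not receive. If the rule is applied to the NEAR arm alone, the two arms are filtered differently. If it is carried over to controls, the article does not say how.

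**Working it through.** **Inputs from the article**

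- Total planned: 30 (2.3).
- NEAR arm: 3 × 5 = 15 (2.3). Control arm: 30 − 15 = 15, by subtraction.
- Visits after therapy: T2 and T3, in both arms (2.3).
- Primary outcomes: GAF and BRIEF Global Executive Composite (3).
- Time points in the treatment-effect test: baseline and completion, that is T1 and T2 (3).

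The article attaches no figure to the rule and gives no effect size, standard deviation, power or dropout for the 30. Beyond the 15 + 15 split there is nothing of its own to reproduce. All rates below are assumptions, shown as ranges.

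**Step 1. What each reading does to a patient with valid T1 and T2 GAF and BRIEF**

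| Reading of the rule | T3 missed | Secondary test unfinished |
|---|---|---|
| Not reassessed at T2 | kept | kept |
| T2 and T3 both required | excluded | kept |
| Both visits and the whole battery required | excluded | excluded |

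The text allows all three readings. The patient has everything the T1-to-T2 contrast needs in every row.

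**Step 2. Patients lost**

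Take all 30 as having valid T2 primary scores. Let m be the share who miss T3 and u the share with an unfinished battery, treated as independent. Then

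kept = 30 × (1 − m) × (1 − u).

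| m | u | Kept | Lost |
|---|---|---|---|
| 10% | 0 | 27.0 | 3.0 |
| 20% | 0 | 24.0 | 6.0 |
| 10% | 10% | 24.3 | 5.7 |
| 20% | 20% | 19.2 | 10.8 |

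Under the T2-only reading in the first row of Step 1, none of these patients is lost.

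**Step 3. Precision**

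With two time points, the Group by Time test is equivalent to a two-sample t-test on change scores. Assume a two-sided 5% level (the article does not state sidedness) and let d be the group difference in standard deviations of change.

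| Per arm | Power, d = 0.8 | Power, d = 1.0 | d detectable with 80% power |
|---|---|---|---|
| 15 | 0.56 | 0.75 | 1.06 |
| 12 (m = 20%, u = 0) | 0.47 | 0.65 | 1.20 |

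At d = 0.8 the cost of m = 20% is about 10 points of power.

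**Step 4. Selection**

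Let a share p of one arm be excluded, and let the mean change of those kept exceed that of those excluded by δ. The full-arm mean is (1 − p) × kept mean + p × excluded mean, so the analysed mean is too high by p × δ. If 3 of 15 NEAR patients are removed and no controls, p = 3/15 = 0.20 and the group difference shifts by 0.2δ. Equal p and equal δ in both arms would cancel. The article fixes neither, so this gives a mechanism and not an estimate of bias.

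**The case against.** The strongest reply is that the rule may mean something narrower. It names no visit and no completeness threshold, and it does not say that data already collected are thrown away. A natural reading is a patient who completes therapy and is never reassessed, and the treatment-effect sentence, which stops at completion, fits that. A reader might infer that one missed T3 or one unfinished test automatically discards a valid T2. The text permits that result but does not state it. The reply turns a fixed rule into an ambiguous one and leaves the ambiguity in place. The opening of the Statistical analysis section also speaks of the end of the study, which could be taken as T3, so the article does not settle the matter elsewhere.

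A reader might also infer that the rule has no meaning for controls. That goes too far. Controls have three evaluations at the same interval, so the rule could be carried over; what is missing is a statement of whether and how.

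Heavier loss among controls is a further tempting inference, because availability for evaluations is an allocation criterion. The article does not say how that criterion is applied, so the direction of any unequal loss is not documented.

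One could also count 16 instruments at two visits, assume 1% non-completion of each, and obtain 1 − 0.99^32 = 0.275, or about 28% excluded. This should carry no weight. The rate is assumed, failures cluster within patients, and the figure needs the harshest reading of the rule.

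Finally, the choice of missing-data model belongs to a fuller document that is not shown, and its absence from the article is not criticised here. The objection that this criterion should not be judged apart from its two neighbours is fair and is taken up in the fix.

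**Conclusion.** The point holds as a badly fixed rule: a post-enrolment exclusion with no defined visit or completeness, worded for the NEAR arm only, which permits the loss of usable primary data. It is a stated criterion and not a detail that the article left out.

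Its size depends on the reading and on rates that the documents do not give. Under the strict reading, 10% to 20% missing T3 among patients with a valid T2 costs about 3 to 6 of 30. At the upper end, with d = 0.8, power falls from 0.56 to 0.47. Under a T2-only reading, a missed T3 costs nothing. Selection on follow-up adds possible bias in a comparison that randomization does not protect, but neither its size nor its direction can be taken from the article. The change should be made; the design does not depend on it.

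**What to change.** Remove this criterion as a ground for exclusion from analysis and replace it with a rule along these lines:

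- Every enrolled patient stays in the assigned group.
- Each primary outcome is analysed with all T1 and T2 data obtained, whether or not T3 or any other test was completed.
- The same rule, worded by visit and by outcome, applies in both arms.
- Patients without T2 are reported as missing, by arm.
- An analysis restricted to completers is shown only as a sensitivity analysis.

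Handle the two neighbouring criteria (programme not achieved, more than three sessions missed) in the same revision. They have no counterpart among controls, so they filter the NEAR arm alone, and changing only the assessment rule would leave the analysed arms unequally selected. This concerns who is analysed, not how attendance is managed.

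The text change is small, but it has consequences. Numbers analysed will differ between outcomes and must be reported for each. The Trial status section (7) gives 26 recruited and 15 who have received NEAR, so anyone already excluded has to be identified and their data reviewed under the new rule. Recruitment was still open at that point. The revision should be dated and made before outcomes are compared.

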Currently, there is a wide range of challenges, and paths for fundamental advances in ASD therapeutics that have reported that this population do not readily generalize and maintain skills. Successful generalization in necessary for an intervention to have benefits in everyday life beyond the original learning environment. CR and SST show only moderate effects and transfer into reals world is insufficient. Thus, a combination of CR and skills groups could help.

In view of all these data, we propose to conduct a study aimed at improving the maintenance and generalization of skills to new situations and environments in this population, by adapting the NEAR method. The main objective is to evaluate the effect of cognitive training combined with the NEAR approach (CT-NEAR), delivered in a social rehabilitation framework, on the global functioning of adolescents with autism. The goal is to reduce the negative impact of impaired cognition on the daily life and to enhance of the global functioning.

NEAR, which is used with a variety of cognitively challenged psychiatric populations, includes computer based cognitive exercises and verbal “Bridging groups” to help patients transfer their practice of cognitive and social skills with real-world situations. Adolescents with ASD require more of a focus on social cognitive skills which is typically provided in the NEAR program. Our adaptation work aims to provide, through these skill-building groups, an opportunity to improve social skills as well as other competencies. Thus, the adaptations would increase focus on improving language pragmatics, ToM, empathy, and attributional style. These adapted “Bridging groups” would also aim to increase the effectiveness of the therapeutic process by encouraging the process of generalization that promotes the application of cognitive skills and compensatory strategies acquired in the sessions to situations outside of the group (53).

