In this study, the experimental group will benefit from cognitive remediation with NEAR, which combines cognitive remediation and social rehabilitation. This program targets a wide range of neuropsychological deficits (attention, visual field, verbal and visual short-term memory, working and long-term memory, planning, problem-solving, inhibition, mental flexibility…) with an expectation that the improvement after program will translate into greater competency in daily life (47, 88).

NEAR method focuses also on adhering to principles of motivation and learning. The impact of motivational factors on the development of social skills and social cognition in ASD are thought to have downstream effects on the development of social cognition (11). Moreover, this method represents an attractive therapeutic tool for young subjects. In a pilot study testing the NEAR program with four preadolescents and adolescents aged 11–15 years with either ADHD or ASD, all participants enjoyed the program. Also, they found it a fun and effective way to learn new strategies, and they found a pleasure of seeing each other again every week. They perceived support and the development of self-help skills (55). NEAR method also integrates the metacognitive dimension that helps the participants to develop the capacity to reflect on their own cognitive processes. Some studies suggest that metacognitive aspects are of particular importance for social abilities in children and adolescents with ASD (89). The sharing time during the Bridging group (difficulties encountered during the exercises, strategies used, link with daily life, …) aims to foster self-esteem, reinforce intrinsic motivation but also to improve their autonomy, social functioning of the participants, and improve pragmatic skills.

From this same perspective, the impact of cognitive remediation on functional outcomes appeared to be significantly greater in studies that also included psychiatric rehabilitation, suggesting that these two therapeutic approaches may act synergistically (90, 91).

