## Trial status

7.

The recruitment of subjects began in July 2021 and still continued. Twenty-six subjects were recruited so far. Fifteen adolescents benefit from cognitive remediation with the NEAR up to now.

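### Patients are allocated by motivation and family availability, and the Group x Time test is read as the treatment effect without accounting for either

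*Protocol article*

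**What the plan says.** The Study design section is open about the design: "Our study is a prospective, experimental, open, and non-randomized controlled trial". Under Participants and screening, "Our study will include 30 patients that will be divided into two groups: NEAR group/ control group", the controls receiving usual care. The same section then says "This allocation of patients between the two groups would be made according to the following criteria". The first criterion is the teenager's motivation. The second reads "Their availability and parent’s one to accompany them to their clinical evaluations and therapeutic sessions". No threshold, ranking or direction is given.

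On motivation, the description of the NEAR method credits it with helping learning and associates it with autonomy and self-esteem. The Discussion adds: "The impact of motivational factors on the development of social skills and social cognition in ASD are thought to have downstream effects" on social cognition. On family involvement, the Discussion says that home tasks carry the programme into the adolescent's everyday life. Participants and screening lists parent involvement among the adherence strategies and excludes patients who miss more than three sessions.

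The Statistical analysis section names GAF and the BRIEF Global Executive Composite (GEC) as primary outcomes. It uses a repeated-measures ANOVA, from baseline to completion, whose Group x Time term is to measure treatment effects. The only adjustment described is a repeat of that model with baseline cognitive scores as covariate, for two measures that differ at baseline.

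**The concern.** A non-randomised comparison can be informative if the variables that decide group membership are either unrelated to outcome or handled in the analysis. Here the allocation variables are known, at least one is described in the article as acting on the kind of skill under study, and neither appears in the model or among the listed baseline assessments.

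If motivated adolescents with available families improve more over about six months whatever care they receive, the Group x Time term will show it as a NEAR benefit. The Background states the main objective as evaluating the effect of CT-NEAR on global functioning, and the analysis as described could not tell that effect from selection.

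**Working it through.** **1. Does the planned model remove the problem?** With two time points, the Group x Time F statistic is the square of the t statistic comparing mean change (completion minus baseline) between groups. A stable difference in level cancels in the subtraction. A difference in rate of change does not, and that is how motivation or family support would be expected to act. Baseline cognitive scores are not a measure of either.

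**2. Is either variable measured?** The assessments cover global functioning, social cognition, neurocognition, pragmatic skills, social skills and self-esteem. None measures motivation for the programme or family availability. The social motivation subscale of the SRS describes a feature of autism, and it is not a covariate either.

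**3. Group sizes.** "The patients included in the NEAR group will be divided into three groups of five patients each": 3 × 5 = 15 in NEAR, leaving 30 − 15 = 15 controls. The article gives no effect size, SD or power, so there is no figure of its own to reproduce.

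**4. How large could the distortion be?** The documents give no correlation between motivation and change, so the following is illustrative. Assumptions: 30 patients; the upper 15 on an allocation score go to NEAR; true treatment effect zero; a t-test on change, two-sided 0.05. Let

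- r = correlation of motivation with change, present in both arms (assumed 0.1 to 0.3);
- a = correlation of the allocation score with motivation (1.0 = complete sorting, 0.5 = loose selection);
- D = expected gap in motivation, in SD, between the upper and lower 15 of 30. The simulation implies D ≈ 0.465 / 0.3 = 1.55; the large-sample value is 2 × √(2/π) = 1.60.

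Spurious difference in SD of change ≈ a × r × D.

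| a | r | a × r × 1.55 | Simulated difference | Simulated rejection rate |
|---|---|---|---|---|
| 0.5 | 0.1 | 0.08 | 0.081 | 5.7% |
| 0.5 | 0.3 | 0.23 | 0.234 | 9.6% |
| 1.0 | 0.1 | 0.16 | 0.155 | 7.0% |
| 1.0 | 0.3 | 0.47 | 0.465 | 24.6% |

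Each row rests on 20,000 runs. With r = 0 the rejection rate was 5.0% to 5.3%, as it should be.

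**5. Scale.** By the normal approximation, 15 against 15 has 28% power for a true difference of 0.5 SD and needs about 1.03 SD for 80%. A distortion at the upper end of the table, 0.47 SD, would be close to that 0.5 SD.

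**6. Can adjustment repair it?** Only in part. If the upper half on motivation goes to NEAR, motivation and group correlate at about 0.8. The variance inflation is then 1 / (1 − 0.8²) = 1 / 0.36 ≈ 2.8, so the standard error of the group term grows by √2.8 ≈ 1.7. Overlap has to be shown before an adjusted estimate is trusted.

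**The case against.** The strongest reply has four parts.

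- **The trial declares itself non-randomised.** True, but the declaration does not change what the Group x Time term estimates. The difficulties set out in the Discussion include drug treatment but not this allocation rule.
- **The prognostic link is thinner than it looks.** A reader might infer that the article calls both criteria predictors of the primary outcomes. It does not. Its statements concern motivation, and they refer to learning, autonomy, self-esteem, social skills and social cognition, not to GAF or GEC. Home tasks belong to the NEAR programme, so they do not show that available families do better under usual care. If motivation only helped patients to profit from NEAR, that would be effect modification and would create no false effect where NEAR does nothing. This stands as a limit on what is known: the illustration needs motivation to predict change in both arms, which is plausible but not stated.
- **The contrast may be small.** All candidates received psycho-education intended partly to raise motivation, and controls must attend evaluations too. The direction of allocation is inferred, although the load of one to two sessions a week falls on NEAR families alone. This argues for the lower rows of the table and does not remove the concern.
- **Trial status.** "Fifteen adolescents benefit from cognitive remediation with the NEAR up to now", with 26 recruited. A reader might infer that the other 26 − 15 = 11 are controls, that the last 30 − 26 = 4 must be controls, and that the rule can no longer operate. The text does not say that the 11 are controls or whether excluded patients are replaced. A rule that has filled one arm has in any case operated.

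An unseen analysis plan is no full answer, because the article itself states the allocation rule, the model and the one covariate adjustment.

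**Conclusion.** The concern holds. Allocation depends on motivation and availability, the article ties motivation directly and availability indirectly to the processes under study, and the stated analysis reads Group x Time as the treatment effect without either. A positive result could not be separated from selection.

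The size cannot be determined from the documents. The span from 0.08 SD (6% false positives) to 0.47 SD (25%) depends on the assumed correlations and on how strictly patients were sorted. It would be wrong to quote 25% as the trial's error rate: that figure needs r = 0.3 and sorting on motivation alone, while the rule has two criteria, one of them logistical. Nor does the argument show that NEAR has no effect, only that this comparison does not isolate one.

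**What to change.** Before analysis, amend the plan as follows.

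1. Fill any control places still open with adolescents who meet the same motivation and availability criteria as the NEAR patients. Randomise only if NEAR places are in fact still open; if all 15 are taken, there is little or no scope for this.
2. Record both criteria for every patient, and mark those classified retrospectively, since such judgements in an open study can themselves be biased.
3. Analyse GAF and BRIEF GEC adjusted for their own baseline value. Add motivation and availability as a prespecified sensitivity analysis, and report the overlap between arms on both.
4. State the result as an association in a comparison confounded by allocation, not as the effect of CT-NEAR, and list the allocation rule among the limitations.

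The cost is an amendment, two extra items to record and a more modest claim. Step 1 may affect only a few patients. At n = 30 with poor overlap, the sensitivity analysis may be imprecise or correct the imbalance only in part, which is why step 4 is needed whatever it shows.
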